### 3. DPP-4 inhibitors

*Nausea*  
*Vomiting*  
*Oedema*  
*Upper respiratory tract infection*  
*Nasopharyngitis*  
*Pain*  
*Osteoarthritis*  
*Headache*  
*Tremor*  
*Asthenia (weakness)*  
*Dizziness*

### 4. GLP-1 receptor agonists

Nausea  
 Vomiting  
 Abdominal pain and distension  
 Diarrhoea or loose stool  
 Discomfort or reaction at injection site  
 Anorexia  
 Hypoglycaemia  
 Gastro-oesophageal reflux disease  
 Headache  
 Dizziness  
 Asthenia (weakness)  
 Increased sweating

### 5. Insulin

Hypoglycaemia  
 Discomfort or reaction at injection site  
 Weight gain  
 Lipodystrophy at injection site

### 6. Metformin

Nausea  
 Abdominal pain  
 Diarrhoea (usually transient)  
 Anorexia  
 Taste disturbance

|                                                                                   |                                                                                                  |                                           |                                                             |                                                  |
|-----------------------------------------------------------------------------------|--------------------------------------------------------------------------------------------------|-------------------------------------------|-------------------------------------------------------------|--------------------------------------------------|
| [figure not shown] | Title:
EndoBarrier TM
Gastrointestinal Liner
Diabetes Trial | Protocol No:
Version 5.0 | Sponsor:
Imperial College
London | Date:
5th March 2018 |
|-----------------------------------------------------------------------------------|--------------------------------------------------------------------------------------------------|-------------------------------------------|-------------------------------------------------------------|--------------------------------------------------|

Other anticipated adverse events in the control group can include hypoglycaemia, peptic ulcer or gallstones due to a change in food intake and weight loss.

#### Other anticipated adverse events

If the patient participates in any of the 3 sub-groups for the mechanistic tests, adverse effects may include discomfort during cannula insertion, bruising at the cannula insertion sites, but this should disappear within a few days after the study visit. Infection around the cannula site is very rare but readily treatable with oral antibiotics in the unlikely event of occurrence. During the insulin clamp tests, hypoglycaemia is very rare and the personnel performing the clamp procedure have been trained to avoid it and treat it appropriately should it occur.

Maximal venesection blood volumes for each sub-group are outlined below. The blood volumes taken over the 24 month time frame should not be associated with impaired iron status but routine haematology blood samples taken at visits 1-15 will be monitored for signs of compromised iron status and treated with iron if deemed appropriate.

EndoBarrier only (no sub-group) = 490ml (355ml year 1, 135ml year 2)

Sub-group 1 fMRI = 695ml (540ml year 1, 155ml year 2)

Sub-group 2 clamps = 1130ml (975ml year 1, 155ml year 2)

Sub-group 3 taste = 695mls (540ml year 1, 155ml year 2)

## **6.7 MRI safety and protection of patients**

The MRI scanner contains a very strong magnet. Therefore, individuals may not be able to have the MRI if they have any type of metal implanted in their body, for example, any pacing device (such as a heart pacer), any metal in their eyes, or certain types of heart valves or brain aneurysm clips. Magnetic resonance imaging metal check list will be completed at each visit to ensure compatibility with MRI scanning.

There is not much room inside the MRI scanner. Some people may be uncomfortable if they do not like to be in close spaces (“claustrophobia”). This is therefore an exclusion criterion for recruitment to the MRI study. If subjects experience discomfort within the scanner despite the measures taken to ensure patient comfort, the patient may request immediate cessation of the procedure with withdrawal from the scanner by ringing the patient alarm bell.

The MRI produces a “hammering noise” but subjects wear earplugs and headphones to prevent discomfort or damage to hearing.

At fMRI study visits, anatomical brain scans will be collected. It should be noted that these scans cannot be viewed as a comprehensive health screening procedure. However, very rarely, unexpected information can be detected which may warrant further investigation. In this event, a report will be sent to the patient's GP, who will arrange further tests and coordinate further care. Significant structural anatomical abnormalities will also preclude the subject from further

|                                                                                   |                                                                                                  |                                           |                                                             |                                                  |
|-----------------------------------------------------------------------------------|--------------------------------------------------------------------------------------------------|-------------------------------------------|-------------------------------------------------------------|--------------------------------------------------|
| [figure not shown] | Title:
EndoBarrier TM
Gastrointestinal Liner
Diabetes Trial | Protocol No:
Version 5.0 | Sponsor:
Imperial College
London | Date:
5th March 2018 |
|-----------------------------------------------------------------------------------|--------------------------------------------------------------------------------------------------|-------------------------------------------|-------------------------------------------------------------|--------------------------------------------------|

participation in the study. The anatomical brain MR scans will be reported by a Consultant Neuroradiologist at Imperial College Healthcare NHS Trust.

## 6.8 Definition of Device-Related Adverse Events

Device-related: any adverse event for which a causal relationship between the device and the event is a reasonable possibility (section 6.9).

The likelihood that the event is device related will be categorized as listed, the device-related “cause” will be categorised as follows:

- **Device Failure or Malfunction:** a device has failed if it is used in accordance with the Instructions for Use, but does not perform or function according to Instructions for Use and negatively impacts the treatment by preventing treatment as intended. Such a failure does not necessarily result in significant adverse outcome.
- **Unanticipated Adverse Device Effect (UADE):** Any serious adverse effect on health or safety or any life-threatening problem or death caused by, or associated with a device, if that effect, problem, or death was not previously identified in nature, severity, or degree of incidence in the investigational plan or application (including a supplementary plan or application) or prior medical literature, or any other unanticipated serious problem associated with a device that relates to the rights, safety, or welfare of subjects. This event needs to be entered into the eCRF SAE pages within 24 hours of the site’s knowledge.

## 6.9 Adverse Event Relationship Definition in EndoBarrier Group

Each Investigator will categorize the types of events as follows:

1 = Definitely related to device: Any event that is associated with the device by timing and physiology, and was caused or contributed to by the device.

2 = Possibly related to device: Any event that is possibly associated with the device timing and physiology, and may have been caused or contributed to by the device.

3 = Definitely related to implant/explant endoscopic procedure: Any event that is associated with the implant/explant by timing or physiology, and was caused or contributed to by the implant/explant endoscopic procedure.

4 = Possibly related to implant/explant endoscopic procedure: Any event that is associated with the implant by timing or physiology, and may have been caused or contributed to by the implant/explant endoscopic procedure.

5 = Not related to device, implant or explant procedure: Any event that, although temporally associated (e.g., occurs during or at some time after implant/explant), was not attributable to the device itself, or to general endoscopic procedures.

|                                                                                   |                                                                             |                                    |                                               |                                            |
|-----------------------------------------------------------------------------------|-----------------------------------------------------------------------------|------------------------------------|-----------------------------------------------|--------------------------------------------|
| [figure not shown] | Title:
EndoBarrier TM
Gastrointestinal Liner
Diabetes Trial | Protocol No:
Version 5.0 | Sponsor:
Imperial College
London | Date:
5 th March 2018 |
|-----------------------------------------------------------------------------------|-----------------------------------------------------------------------------|------------------------------------|-----------------------------------------------|--------------------------------------------|

6 = Pre-existing or independent condition: Any event, although temporally associated, that was attributable to a pre-existing or independent condition.

7 = Unknown: The relationship of the event to the device, or procedure is unknown.

8 = Other: Any event that cannot be classified in any of the above categories.

## 6.10 Adverse Device Effect (ADE)

An Adverse Device Effect (ADE) is any untoward and unintended response to a medical device. This definition includes any event resulting from insufficiencies or inadequacies in the instructions for use or the deployment of the device. This definition includes any event that is a result of a user error.

### Endobarrier group

*1. During the implant procedure, the anticipated adverse events may include:*

- Dizziness
- Fever
- Gastroenteritis
- Headache
- Hyper/hypotension
- Liver chemistry changes
- Pancreatic chemistry changes

*2. During the implant period, the anticipated adverse events may include:*

- Vitamin and Mineral Deficiency
- Dehydration
- Constipation
- Bloating
- Diarrhea
- Infection
- Flatulence
- GERD
- Esophagitis
- Pseudopolyps
- Nausea/vomiting
- GI pain/cramping
- Peptic ulcer disease
- Duodenitis
- Local inflammatory tissue reaction
- Flank/Back pain
- Alopecia
- Dizziness

|                                                                                   |                                                                                                  |                                           |                                                             |                                                  |
|-----------------------------------------------------------------------------------|--------------------------------------------------------------------------------------------------|-------------------------------------------|-------------------------------------------------------------|--------------------------------------------------|
| [figure not shown] | Title:
EndoBarrier TM
Gastrointestinal Liner
Diabetes Trial | Protocol No:
Version 5.0 | Sponsor:
Imperial College
London | Date:
5th March 2018 |
|-----------------------------------------------------------------------------------|--------------------------------------------------------------------------------------------------|-------------------------------------------|-------------------------------------------------------------|--------------------------------------------------|

Fever  
 Gastroenteritis  
 Headache  
 Hyper/hypotension  
 Liver chemistry changes  
 Pancreatic chemistry changes

*3. During and after the explant, the anticipated adverse events may include:*

Alopecia  
 Dizziness  
 Fever  
 Gastroenteritis  
 Headache  
 Hyper/hypotension  
 Liver chemistry changes  
 Pancreatic chemistry changes

All of these potential risks are treatable and should not result in a life-threatening situation if a subject is treated promptly. To minimize the chances of a life-threatening situation, each Investigator will discuss all of the signs and symptoms that each subject should watch for. Additionally, each subject will be sent home with a card that will also describe the signs and symptoms to watch for. If they experience any of the signs and symptoms described by their Investigator, they should be instructed to call them immediately, and he will instruct them if they should come to the hospital for treatment.

Insertion and removal of the EndoBarrier device is performed under fluoroscopic x-ray guidance. Each Investigator will be trained in the implantation and removal of the EndoBarrier Gastrointestinal Liner to minimise the exposure time to the x-rays. Mean x-ray exposure time in a previous EndoBarrier research study was 7 minutes for insertion (range 1-20 minutes) and 1.5 minutes for removal (range 0-15 minutes). The constraint (maximum effective dose) for the whole procedure (implant and explant) is 9 mSv which is equivalent to 3.3 years natural background radiation in the UK (2.7mSv/year background) and results in a cancer risk of 1 in 2200 for a healthy 40 year old (5% per Sv risk factor).

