### 2.3 Safety objective

- To evaluate the safety of the EndoBarrier and frequency of adverse events

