## 2.5 Secondary Endpoints

- HbA1c of less than 6% (or 42 mmol/mol)
- Blood pressure below 135/85 mmHg
- Absolute weight loss greater than 15%
- Reduction in dose/or number of medications
- Frequency of Adverse Events
- Cost of interventions and related health and social care
- QALYs accrued (calculated from area under the EQ-5D curve)
- Incremental cost per QALY within the trial period and over the long-term

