### **Visit 6, 7, 9, 11**

The following will be performed:

- Body measurements including weight and waist circumference (5.5.8, 5.5.9)
- Vital signs (5.5.7)
- Routine chemistry and haematology (5.5.10)
- Adverse events (6)
- Medical history/medication changes (5.5.4)
- Dietitian follow up (5.5.3)
- Diabetologist/Endocrinologist diabetes review (5.5.1)
- Health Economics questionnaires (Visit 6 and 7 only) (5.5.4)
- Follow up appointment with gastroenterologist (Treatment arm only) (5.5.2)
- Preparation for EndoBarrier Removal (Visit 9 Treatment arm only) (5.5.2)
- EndoBarrier Removal (Visit 11 Treatment arm only) (5.5.2)
- Gastric and small bowel biopsies during EndoBarrier Explant (Treatment arm only) (5.5.2)

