## 6 ADVERSE EVENTS (AE)

An AE is any untoward medical occurrence in a patient or clinical trial subject administered a medicinal product and which does not necessarily have a causal relationship with this treatment. An AE can therefore be any unfavourable and unintended sign (including an abnormal laboratory finding), symptom, or disease temporally associated with the use of the trial device/procedure, whether or not considered related to the treatment.

All adverse events that occur during this study will be recorded on the adverse event case report forms.

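### Endoscopy is scheduled in the device arm only, so part of any between-arm difference in mucosal adverse events may be detection, and the protocol provides no record of how a finding was made

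*Protocol*

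**What the plan says.** **Endpoint.** Section 2.3 gives the safety objective as "To evaluate the safety of the EndoBarrier and frequency of adverse events", and section 2.5 lists "Frequency of Adverse Events" as one secondary endpoint. Neither divides events by seriousness, relatedness or mode of detection.

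**What is recorded.** Section 6 states: "All adverse events that occur during this study will be recorded on the adverse event case report forms". Its definition covers "any unfavourable and unintended sign (including an abnormal laboratory finding), symptom, or disease temporally associated with the use of the trial device/procedure", and an event counts whether or not it is thought related to treatment.

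**Who is examined.** The section 5.4 visit lists and the EndoBarrier-only block of Table 2 place the implant (visit 4) and removal (visit 11) in the device arm alone, each with biopsies; the visit 11 entry reads "Gastric and small bowel biopsies during EndoBarrier Explant (Treatment arm only)". Section 5.5.2 specifies eight biopsies on each occasion, four of them for histology, and says that those at implant are taken before the device goes in. No control endoscopy is scheduled. Gastroenterologist review is likewise "Follow up appointment with gastroenterologist (Treatment arm only)".

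**What is expected.** The section 6.10 list that opens "2. During the implant period, the anticipated adverse events may include" includes oesophagitis, pseudopolyps, peptic ulcer disease, duodenitis and local inflammatory tissue reaction. Section 6.6 states: "Other anticipated adverse events in the control group can include hypoglycaemia, peptic ulcer or gallstones due to a change in food intake and weight loss".

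**The concern.** Oesophagitis, duodenitis and peptic ulcer can be present without symptoms, and are then seen only if someone looks. Every device patient is looked at twice by protocol. A control patient is looked at only if symptoms lead to an endoscopy outside the protocol. If such findings are entered as adverse events, equal true rates will produce unequal recorded rates.

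The implant endoscopy adds a second route. Screening includes no endoscopy, so there is no mucosal baseline, while adverse event reporting starts at visit 2. A lesion seen at visit 4 before the device is placed cannot be a device effect, yet it can enter the device-arm count and has no possible counterpart among controls.

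At stake is the reading of the safety endpoint. A reader of the trial report could take a detection difference for harm, and would have no recorded variable with which to separate the two.

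**Working it through.** **1. Is ascertainment unequal?** Yes, in depth of examination. Two scheduled endoscopies with histology stand against none. The number of adverse event visits is not unequal: Table 2 marks adverse event reporting for all patients at every visit from 2 to 15.

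**2. Which listed lesions does this affect?** Of the 24 event types listed in section 6.10 for the implant period, five are mucosal or local tissue findings.
- Peptic ulcer disease: anticipated in both arms (6.6 and 6.10), so affected.
- Oesophagitis and duodenitis: listed for the device arm only, but plausible in either arm, so affected.
- Pseudopolyps and local inflammatory tissue reaction: plausibly true effects of the anchor, so not counted as artefact.

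**3. Does relatedness coding repair it?** No. The endpoint is not restricted by relatedness, and the arms use different scales: six categories in section 6.4, eight in section 6.9. Both have a category for pre-existing or independent conditions, but neither records how a finding was made.

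**4. How large could it be?** The protocol gives no lesion prevalence and no detection rate, so there is no plan figure to reproduce. What follows is an illustration. The only input from the protocol is 80 per arm (section 4.1). Assumptions:
- the same true prevalence *q* in both arms;
- every lesion in the device arm is found and recorded;
- a fraction *s* of control lesions is found through symptoms.

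Recorded proportions are p₁ = q and p₂ = q·s, so the spurious difference is q(1 − s). The chance of a two-sided 5% result for that one event term is approximately

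Φ{ [ (p₁ − p₂) − 1.96·√(2p̄(1 − p̄)/80) ] / √([p₁(1 − p₁) + p₂(1 − p₂)]/80) }, with p̄ = (p₁ + p₂)/2.

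Worked case, q = 10% and s = 30%: p₁ = 0.10, p₂ = 0.03, p̄ = 0.065. The two standard errors are 0.0390 and 0.0386, and (0.07 − 1.96 × 0.0390)/0.0386 ≈ −0.17, which gives about 43%.

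| True prevalence q | Control detection s | Patients recorded, device vs control | Spurious difference | Chance of false significance, that term |
|---|---|---|---|---|
| 5% | 10% | 4 vs 0.4 | 4.5 points | 41% |
| 5% | 30% | 4 vs 1.2 | 3.5 points | 24% |
| 5% | 50% | 4 vs 2.0 | 2.5 points | 13% |
| 10% | 10% | 8 vs 0.8 | 9 points | 71% |
| 10% | 30% | 8 vs 2.4 | 7 points | 43% |
| 10% | 50% | 8 vs 4.0 | 5 points | 22% |
| 20% | 10% | 16 vs 1.6 | 18 points | 96% |
| 20% | 30% | 16 vs 4.8 | 14 points | 75% |
| 20% | 50% | 16 vs 8.0 | 10 points | 42% |
| any | 100% | equal | 0 | no excess |

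The normal approximation is rough with so few control events, and an exact test would reject less often. The differences in points do not depend on it.

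**5. Effect on the proportion with any adverse event.** If a share *b* of patients has some other event, independently, the difference shrinks to (1 − b)·q·(1 − s). With q = 20% and s = 10% to 30%:
- b = 30%: 0.7 × 0.2 × 0.9 = 12.6 points, down to 0.7 × 0.2 × 0.7 = 9.8 points.
- b = 80%: 0.2 × 0.2 × 0.9 = 3.6 points, down to 0.2 × 0.2 × 0.7 = 2.8 points.

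The distortion therefore matters most for single mucosal terms, and less for the overall proportion when other events are common.

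**The case against.** **No between-arm test of adverse events is laid down.** The efficacy objectives speak of comparing; the safety objective speaks of evaluating. Only the general sentence on secondary outcomes in section 8.2 implies a test, and tabulation belongs in the SAP, which is not at hand. This stands in part. However, an SAP can separate findings by mode of detection only if that mode is recorded, and the protocol provides for no such record.

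**Nothing says that silent findings become adverse events.** Biopsies are sent for histology and RNA work, not to the adverse event form. Laboratory abnormalities count only if clinically important (6.5), and examination findings are recorded only if abnormal and clinically significant (5.5.4). The lesions appear only under the implant period, not in the lists for the implant procedure or the explant. This is fair: the definition and the list make recording likely but do not establish it.

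**True rates may differ.** The device arm receives omeprazole and H. pylori testing (5.5.2, 5.5.16), which could lower its acid-related lesions. That could mask the detection effect. It would not make the comparison interpretable.

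**Stronger readings that a reader might infer, which the documents do not support.**
- That device-arm events are inflated by 1/(1 − 4/24) = 1.20 to 1/(1 − 5/24) = 1.26. This treats a list of names as event frequencies and counts plausible device effects as artefact. The same method applied to peptic ulcer, the only lesion documented for both arms, gives 1/(1 − 1/24) = 1.04, and it has no better basis.
- That gastroenterologist reviews add to the bias by creating extra reporting occasions. They fall on visits where adverse events are collected in both arms.
- That the endpoint should be limited to events elicited by a common question. This would drop laboratory-detected events (6.5) and those from unscheduled visits (5.4), and would remove silent but real device lesions from the comparison.

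**Conclusion.** The point holds within limits. Scheduled endoscopy and histology in one arm, together with a single undivided endpoint and a wide event definition, allow detection to contribute to a between-arm difference in two groups of findings: mucosal lesions possible in either arm (peptic ulcer, and plausibly oesophagitis and duodenitis), and lesions already present at the implant endoscopy. The detection component works against the device.

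Its size cannot be derived from the protocol. Under equal true prevalence of 5% to 20% and control detection of 10% to 50%, the spurious difference for one lesion type is 2.5 to 18 points. These inputs are assumptions, and the result also presumes that incidental findings are recorded as adverse events. Serious events are less affected.

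It does not follow that an excess of adverse events in the device arm would be artefact. Unequal endoscopy is inherent in a comparison without a sham procedure, so the remedy lies in recording and analysis.

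**What to change.** 1. Add one eCRF item to the adverse event form: *first identified only at a protocol endoscopy or biopsy (yes/no)*. Back-fill it from source documents for events already entered.
2. Keep the full table of all adverse events by arm.
3. Add a between-arm comparison that excludes only asymptomatic findings flagged yes. Laboratory-detected events, events from unscheduled visits and all SAEs stay in.
4. List the flagged findings in a descriptive device-arm table. Show those seen at the implant endoscopy before device placement separately, as pre-existing.

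The cost is one data field, some back-filling, a sentence of endpoint or SAP wording and one extra safety table. The flag needs a judgement where a finding was also symptomatic; such findings stay in the comparison. No safety information is removed.
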